### Study Setting and Population

#### Facility Selection Process

The study is being conducted in 5 public health facilities offering routine MCH services within Kisumu and Siaya Counties in Kenya. The facilities were selected based on high HIV prevalence areas, existing infrastructure, established rapport, and discussions with the Kenyan Ministry of Health and the local government of Kisumu County.

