#### Randomization

Block randomization using a 1:1 allocation in random-sized blocks stratified by recruitment site is being used to ensure a balanced allocation of each arm within sites. Before randomization, study nurses ensure all routine PrEP initiation services and study enrollment procedures are complete. Treatment allocation (mWACh-PrEP or SOC) for each consented participant is done by the study nurses within the individual’s health facility using Research Electronic Data Capture (REDCap; Vanderbilt University). The randomization code is stored in an electronic format, and once assigned, it is unblinded. The randomization key for the database is restricted to the data manager and statistician.

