### Data Analyses

#### Sample Size

The sample size was calculated to detect a difference between trial arms dependent on the frequency of PrEP adherence in the SOC arm of the cohort. Prior data from our PrEP in pregnancy studies indicate that the frequency of detectable PrEP drug levels is approximately 50% among pregnant women who initiate PrEP in MCH clinics within fully programmatic settings [12]. Since this study will exclusively enroll women who initiate PrEP in MCH, we anticipate that adherence will be similar or slightly higher. Assuming a PrEP adherence estimate of 50% in the SOC arm at 6 months post partum and a sample size of 600 (randomized 1:1), we will have 80% power to detect a minimum detectable difference of 12% between arms in PrEP adherence in the mWACh arm, assuming 15% attrition and a 2-sided test with a Cronbach α of .05 (Table S2 in Multimedia Appendix 1).

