#### Statistical Methods and Analyses

The primary outcome, PrEP adherence at 6 months post partum, will be assessed in an intention-to-treat analysis comparing randomization arms mWACh-PrEP versus SOC. Enrollment characteristics will be compared between randomization arms to assess the balance between arms and control for any imbalanced factors. Based on a previous study of directly observed dosing conditions, we will use a hair TFV concentration cutoff of 0.038 ng/mg (corresponding to 7 doses/week) as the threshold of detection for the primary adherence outcome measured at 6 months post partum (detectable/nondetectable binary outcome) [52]. Protective PrEP drug level thresholds for cisgender women have not been established; however, current WHO and Kenyan national guidelines recommend daily (7 doses/week) oral PrEP for cisgender women. A log-binomial regression model will be used to estimate the relative risk, adjusting for any imbalances in baseline demographic, clinical, or behavioral characteristics between arms. Missing primary outcomes or loss to follow-up will be assumed nonadherent. To evaluate the sustained effect of mWACh-PrEP on PrEP-taking habits after the SMS text messaging intervention ends, the same model will be used to analyze our secondary outcome of PrEP adherence at 9 months post partum (3 months after cessation of mWACh-PrEP messaging).

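### Randomisation is stratified by site, but the stated adjustment rule will not bring site into the primary model, so the test is mildly conservative if adherence differs between the five clinics

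*Protocol article*

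**What the plan says.** The Randomization section of the protocol article makes site the stratification factor: "Block randomization using a 1:1 allocation in random-sized blocks stratified by recruitment site is being used". The Facility Selection Process section gives the number of strata: "The study is being conducted in 5 public health facilities offering routine MCH services within Kisumu and Siaya Counties in Kenya".

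Statistical Methods and Analyses sets out how covariates are chosen: "Enrollment characteristics will be compared between randomization arms to assess the balance between arms and control for any imbalanced factors". It then gives the primary model: "A log-binomial regression model will be used to estimate the relative risk, adjusting for any imbalances in baseline demographic, clinical, or behavioral characteristics between arms". Site is not named as a model term anywhere in the article. The same model is to be reused for adherence at 9 months post partum, so the point applies to both analyses.

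**The concern.** Blocking within site takes differences between clinics out of the comparison of arms. A model without site still counts those differences as error. Its standard error for the log relative risk then exceeds the true sampling variation, the confidence interval is wider than the design warrants, and the test rejects less often than its nominal level.

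The covariate rule cannot correct this. It looks for imbalance between arms, and the blocks keep site balanced apart from incomplete final blocks. It also covers demographic, clinical and behavioral characteristics, and site is none of these. The one factor on which the randomisation was built is therefore the one the rule is least likely to select. At stake is a little precision and power.

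**Working it through.** **Inputs from the article.** 300 women per arm, five sites, 50% adherence under standard of care, a 12-point difference (62%, so relative risk 0.62/0.50 = 1.24), 15% attrition, two-sided 5% level. Evaluable per arm: 300 × 0.85 = 255, or 51 per arm per site if sites are equal.

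**Assumptions.** Equal site sizes, a common relative risk across sites, and site-specific adherence evenly spaced around 50%. The article gives no site-level rates, so a range of spreads is shown.

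**Step 1: the plan's own power.** Pooled-variance normal approximation, with mean proportion 0.56:

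- null SE = √(2 × 0.56 × 0.44 / 255) = 0.0440
- alternative SE = √((0.25 + 0.2356) / 255) = 0.0436
- power = Φ((0.12 − 1.96 × 0.0440) / 0.0436) = 78.1%

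The detectable difference at 80% power is 12.3 points, which rounds to the stated 12. The stated figure is reproduced to within rounding.

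**Step 2: excess of the standard error under no effect.** With n per arm, mean adherence p and between-site variance V:

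- variance assumed without site: 2p(1 − p) / (p²n)
- true variance under site-stratified allocation: 2[p(1 − p) − V] / (p²n)
- ratio of standard errors at p = 0.5: √(0.25 / (0.25 − V))

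The type I error that follows is 2[1 − Φ(1.96 × ratio)].

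| Site spread | V | SE too large by | Type I error |
|---|---|---|---|
| none | 0 | 0% | 5.0% |
| 45–55% | 0.00125 | 0.3% | 4.9% |
| 40–60% | 0.005 | 1.0% | 4.8% |
| 35–65% | 0.01125 | 2.3% | 4.5% |
| 30–70% | 0.02 | 4.3% | 4.1% |

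At relative risk 1.24 the excess is slightly larger: 1.3% for 40–60% and 5.4% for 30–70%.

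**Step 3: power, simulated.** 51 per arm per site, relative risk 1.24. The log relative risk without site is compared with the Mantel-Haenszel relative risk by site.

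| Site spread | Without site | By site |
|---|---|---|
| 45–55% | 77.5% | 78.2% |
| 40–60% | 77.7% | 79.3% |
| 35–65% | 77.9% | 80.1% |
| 30–70% | 78.6% | 82.2% |

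With identical sites the two analyses agree to within simulation error. The large-sample formula gives somewhat smaller gains: 77.5% to 78.2% at 40–60%, and 78.4% to 81.3% at 30–70%. Part of the simulated gap comes from the discreteness of binary counts.

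**Step 4: two variants.**

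- All 300 per arm analysed (60 per arm per site), with 50% and 62% taken as the rates in that full set: 84.8% against 85.2% at 40–60%.
- A maximum-likelihood log-binomial model with site terms, at 51 per arm per site: 80.8% at 40–60% and 88.2% at 30–70%. This larger gain depends on the relative risk being the same at every site. In the 30–70% case the model's standard error is slightly below its sampling standard deviation (0.0697 against 0.0713), so the Mantel-Haenszel figures are the safer guide.

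**The case against.** The strongest reply is that a condensed article need not list every covariate, that it refers to a statistical analysis plan, and that it never says site is excluded. This stands in part: the unseen plan may well include site. But the article does more than stay silent. It states a selection rule, and that rule works against the design, so naming site would mean going beyond what is published.

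The reply on size also carries weight. The clinics lie in two counties and deliver PrEP under the same national guidelines, so wide differences in adherence cannot be presumed. At moderate spreads the loss is about two points of power or less.

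Four stronger readings are tempting, and the documents do not support them.

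- A reader might infer bias or false positives. The error runs the other way: the test is conservative.
- A reader might infer that the trial is already short of its stated power. Under the article's own inputs the 80% reproduces to within rounding. Whether counting missing outcomes as nonadherent changes this is a separate question and does not depend on site.
- A reader might infer that site terms would absorb differences between the nurses who handle the messages. Only the intervention arm gets messages, so such differences would make the effect of the intervention vary by site. That is an interaction, which site main effects do not remove.
- A reader who simulates the test might attribute all of a rejection rate below 5% to the omitted site term. With identical sites the simulated rate is already about 4.6%, because the counts are discrete.

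**Conclusion.** The point holds as a modest loss of efficiency. The design stratifies by site, and the stated covariate rule will essentially never bring site into the model. If clinics differ, the standard error under no effect is about 1% too large at a 40–60% spread and 4–5% too large at 30–70%. The power forgone against Mantel-Haenszel by site is about 0.7 points at 45–55%, 1.6 at 40–60%, 2.2 at 35–65% and 3.6 at 30–70%. If sites are alike, the loss is nil. These sizes rest on five equal sites, a common relative risk, 51 evaluable per arm per site and an assumed spread that the article neither gives nor rules out. The analysis as written remains valid. The change is worth making because it recovers precision without recruiting anyone.

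**What to change.** Prespecify recruitment site as a fixed term (four indicators) in the log-binomial model for the 6-month primary outcome and the 9-month secondary outcome, whatever the baseline comparison shows.

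State in advance what will be done if that model does not converge, for example modified Poisson regression with robust standard errors or the Mantel-Haenszel relative risk by site. The fallback matters because a log link becomes unstable when fitted probabilities approach 1. In the 30–70% case the highest site in the intervention arm is already at 0.70 × 1.24 = 86.8%.

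The cost is a sentence or two in the analysis section and 4 degrees of freedom out of 600 participants. Site is known at randomisation, so no new data are needed. The change should be fixed before outcome data by arm are examined.

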#### Qualitative Analyses

Focus group discussions and semistructured in-depth interviews will be conducted to evaluate potential barriers and facilitators to the acceptability and feasibility of mWACh-PrEP implementation within routine ANC delivery settings (Figure 4). To evaluate personal experiences with the mWACh-PrEP intervention, a purposively selected sample of study participants will be recruited to participate in in-depth interviews. In-depth interviews will explore community, dyadic, and individual factors influencing decision-making and how these influence individual perceptions of and experiences with mWACh-PrEP use. To gather perspectives on the mWACh-PrEP scale-up, we will invite the study’s community advisory board (CAB) and county-level health officials overseeing ANC-PrEP programs to participate in focus group discussions. These focus group discussions will elicit perspectives on foreseeable barriers and facilitators of larger-scale implementation of mWACh-PrEP based on individual, community, and health system factors.

Discussions will be conducted in English, Kiswahili, or Luo depending on participants' preferences and be guided by prepiloted topic guides with the flexibility to explore additional probes and newly emerging content as necessary. All in-depth interviews and focus group discussions will be audio recorded, transcribed, and translated to English for analysis as necessary. Thematic analysis will be used to identify key elements of the patient/provider experience, including convenience, comfort level, and satisfaction of the mWACh-PrEP model, that influence intervention acceptability, feasibility, and potential scale-up.

**Figure 4 figure4:**
[figure not shown]
Schematic of qualitative purposive stratified sampling approach (N=70). PrEP: pre-exposure prophylaxis.

#### Cost-effectiveness Analysis

##### Overview

We will project the cost-effectiveness of implementing mWACh-PrEP intervention within ANC compared to the SOC per averted disability-adjusted life year (DALY) using a payer perspective and collect intervention costs from expense reports, staff, and expert interviews. Costs will be divided into mutually exclusive categories, including personnel, equipment, supplies, buildings and overhead, and start-up. We will convert the local currency, Kenyan shillings, to US dollars. Sensitivity analyses will be conducted to identify influential assumptions.

##### Costing

Time and motion observation of intervention activities will be conducted to calculate staff time and resources necessary for the mWACh-PrEP intervention. A research assistant (RA) will collect data on the time and motion of patient/provider interactions to inform costs and productivity assumptions. The RA will also conduct a survey with health care workers to assess daily responsibilities associated with the mWACh-PrEP intervention, including time to send and respond to client SMS text messages and routine service provision. Research time (eg, administering study questionnaires) and other research costs will be separated from programmatic costs.

##### Modeling

We will parameterize a previously developed mathematical model with cost and outcome data from the mWACh-PrEP trial and project the averted HIV infections, HIV-related deaths, and DALYs associated with scaling up the mWACh-PrEP intervention in Kenya. We will calculate the incremental cost-effectiveness ratio as the difference in costs divided by the difference in effects (DALYs) for the intervention compared to SOC over a 20-year period. Costs and benefits will be discounted annually at 3%.

#### Secondary and Exploratory Analyses

Secondary outcome analyses will include sustained PrEP adherence by determining levels of detectable TFV in the hair at 9 months post partum, adherence cofactors, STI incidence, and prevention-effective adherence (time-varying alignment of adherence with risk behaviors). Exploratory analyses will include HIV incidence, perinatal outcomes, and expedited partner treatment outcomes by randomization arms (Table S3 in Multimedia Appendix 1).

### Ethics Approval

Ethical approval was obtained from the institutional review board of the University of Washington (STUDY00010797) and the Kenyatta National Hospital Ethics and Research Committee (P319.05/2021). This study was registered at ClinicalTrials.gov. (NCT04472884). Any critical protocol deviations, adverse events, and future modifications will be communicated promptly to these organizations. Additional permissions will be sought from all participating clinical sites.

### Informed Consent

A written informed consent before recruitment is administered to all study participants, with each receiving a copy of the signed form. Additional permission will be obtained for audio recording and note-taking during the qualitative interviews.

All participants are informed that their participation is voluntary, and they can stop receiving the SMS text messages at any time by contacting the study staff or texting “STOP,” which will cease communication between the study staff and the participant. All study staff is trained in protecting human participants and the clinical and emotional needs of pregnant and postpartum women on PrEP. The MWACh system is point-to-point encrypted; therefore, only study team members can access it through a password-protected laptop stored in a locked office. All data are deidentified and kept in password-protected databases in a locked study office that is accessible only to study personnel.

#### Patient and Public Involvement

A CAB has been established in Kisumu County to review the study objectives, methodology, and other study activities. The team comprises local community leaders, women from the community, the Kenyan Ministry of Health, and county health representatives from MCH departments. The CAB is anticipated to meet 2 times per year to review this study’s progress. An external advisory panel (EAP) has been established to oversee the data and safety of study participants by reviewing study aims, statistical analysis plan, and progress. EAP meetings will be routinely convened to review study enrollment, retention, data missingness, and pooled study outcomes. Study results will be disseminated through peer-reviewed journals, technical reports, policy briefings, and oral presentations at relevant local and international conferences. Additionally, we will present results to clinical experts and policy advisors at the local county level, the Kenyan Ministry of Health, and the WHO. Routine hybrid meetings in the form of progress updates with CABs engaged in the study activities, facility staff, and study collaborators will be conducted to share study progress and findings.

## Results

Study enrollment began in March 2022 and is projected to continue until July 2023, with patient participant follow-up through March 2024. The study results are expected to be reported in 2025.

## Discussion

### Anticipated Findings and Implications

This intervention study aims to determine the effect of the mWACh-PrEP tool on PrEP adherence among pregnant and breastfeeding women at high risk for HIV acquisition who initiate PrEP during ANC. The primary outcome is adherence at 6 months, while the secondary outcomes include sustained adherence at 3 months after cessation of the SMS text messaging intervention and other HIV and MCH indicators. This is the first intervention that aims to enhance PrEP adherence among women in the peripartum period research, and we anticipate that our findings will inform clinical practice for PrEP delivery during the peripartum period by providing effectiveness data on an mHealth PrEP adherence tool tailored for the peripartum period.

### Study Strengths and Limitations

This is the first intervention study aiming to improve PrEP adherence among peripartum women using an IMB-guided approach tailored to pregnant and postpartum women on PrEP for HIV prevention. The development of adherence strategies for periods during and after pregnancy can have implications for other daily medications taken during pregnancy and the postpartum period when medication side effects overlap with typical symptoms, and life events pose challenges to sustained adherence. Furthermore, collected microcosting data will guide researchers and policy makers on the cost of scale-up and use of mHealth and the IMB-informed approach.

Daily oral tenofovir disoproxil fumarate (TDF)/emtricitabine is currently the only medication with a label indication as PrEP in Kenya and the only regimen recommended by the WHO for cisgender women. While several novel PrEP agents are being tested, including long-acting injectable cabotegravir (CAB-LA) [53], forthcoming results are still years away, and it will take longer for CAB-LA to reach pregnant or lactating women as there is no safety evaluation underway in these populations. Similarly, event-driven PrEP (ED-PrEP) is not approved by the US Food and Drug Administration. Moreover, WHO guidelines explicitly state that ED-PrEP is not appropriate for cisgender women, citing effectiveness concerns in this group [54]. Therefore, daily oral TDF/emtricitabine will likely remain the PrEP SOC for pregnant and breastfeeding women for several years. Because this is a programmatic RCT, the characterization of some secondary and exploratory outcomes will be limited. This design was intentional to optimize program/policy relevance. Costing data will be collected to understand how additional time spent by nurses on the intervention in already busy health facilities may potentially affect scale-up.

### Dissemination Plan

To provide insights on the effects of mWACh-PrEP, we will communicate the study protocol, progress report, and results to the scientific community and policy makers. This will guide the clinical management of pregnant women who choose to initiate PrEP, informing future scale-up of the intervention as a population-level program. Dissemination of the results will potentially improve communication between researchers, ethical bodies, and policy makers and strengthen collaborations between participating partners through technical reports and policy briefings. For the scientific community, we will publish our findings in peer-reviewed journals and present them at international scientific conferences. Presentations and progress reports regarding the study will be shared with study participants and presented to the public at the facility level and to the Kenyan Ministry of Health.

### Conclusion

This study will inform clinical practice and contribute to advancing strategies to enhance PrEP and other daily medication adherence during pregnancy and the postpartum period, which are both critical periods for MCH. If our mWACh approach positively affects MCH outcomes (eg, birth and infant outcomes), it could be readily integrated into other mHealth platforms aiming to improve MCH in the future. The study will also contribute to an mHealth adherence tool for pregnant women on PrEP with the goal of enhancing PrEP use and ultimately reducing HIV incidence in this important population that is disproportionately affected by HIV.

## Appendix

Multimedia Appendix 1 Tables S1-S3.

## Abbreviations

ANC: antenatal care
ART: antiretroviral therapy
CAB: community advisory board
CAB-LA: long-acting injectable cabotegravir
DALY: disability-adjusted life year
DBS: dried blood spots
DHS: Demographic and Health Survey
EAP: external advisory panel
ED-PrEP: event-driven pre-exposure prophylaxis
HAL: Hair Analytical Laboratory
IMB: Information-Motivation-Behavioral Skills
IPV: intimate partner violence
MCH: maternal and child health
mHealth: mobile health
mWACh: Mobile Solutions for Women’s and Children’s Health
PrEP: pre-exposure prophylaxis
RA: research assistant
RCT: randomized controlled trial
REDCap: Research Electronic Data Capture
SOC: standard of care
STI: sexually transmitted infection
TDF: tenofovir disoproxil fumarate
TFV: tenofovir
TFV-DP: tenofovir diphosphate
WHO: World Health Organization
